#### Proposed primary outcome measure

The *assessment of parent–child interaction (APCI)* [32, 33] was developed for at-risk families and is being used for the first time in an RCT to evaluate music therapy interaction processes in paediatric oncology. The APCI assesses the child-significant other dyad interaction based on three dimensions: mutual attunement, nonverbal communication, and emotional parental response. The goal is that the same significant other attends all APCI sessions. In exceptional cases, a change of significant others is permitted. The training manual [32] includes theoretical considerations, state-of-the-art literature considering the APCI, and information on how to plan, analyse, and report the collected information. The assessment sessions follow a manualized procedure: (1) welcome and exploration of the room and instruments; (2) the sequence of four different practice sessions, which are first carried out together with the therapists and subsequently by the child-significant other dyad alone; and (3) the farewell. The four sequences consist of (Ex1) playing a crescendo and decrescendo together, (Ex2) taking turns in making music and handing over the musical action, (Ex3) mutual leading and following in music, and (Ex4) free improvisation. Video evaluation is used to assess the three APCI dimensions which are transferred to the APCI online portal for the calculation of a total APCI score, subscores for each dimension, and further statistical analyses. The APCI total score is determined from 16 APCI profiles, which are made up of the following observations: (1) mutually attuned (M)/not mutually attuned (N), (2) clear nonverbal communication (C)/unclear nonverbal communication (U), (3) supportive parenting (S)/lack of parenting support (L), and (4) independent child (I)/dependent child (D). The APCI shows good to satisfactory interrater reliability and test-re-test reliability both in the overall score and in its subscores [33]. In our feasibility RCT, the raters of the APCI diagnostics were trained and certified by [name] (Training Lead & Senior Clinical Therapist at Chroma Arts Therapies, UK) to use the APCI. During the study, they will be supervised by [name] and [name] (Associate Professor of Music Therapy, Aalborg University, Denmark). Two independent student raters will rate one of the two first APCI session, and the final APCI session, for manual adherence.

#### Proposed secondary outcome measure

The *goal attainment scaling (GAS)* asks for the subjective goals of the children and significant others in free text. These are classified using the Bern Inventory of Therapy Goals (BIT-T) [44]: (1) coping with specific problems and symptoms, (2) interpersonal goals, (3) well-being, (4) existential issues, (5) personal growth, and (6) residual category. In [36] coding an extended sample of client treatment goals, the BIT-T proved to have a good interrater reliability, identified differences between diagnostic groups, and showed meaningful relations to standardized intake measures [45].

The quality of life will be assessed using the *KINDL Children and Adolescents Version, Oncology Module* [46, 47]. KINDL measures psychological well-being, social relationships, physical functioning, and daily activities within the last week using 40 items. The KINDL shows very good to satisfactory internal consistency and test-re-test reliability both in the overall score and regarding its dimensions. The questionnaire is a validated assessment for children and adolescents aged 3 to 17 and is accompanied by master’s students in psychology. It is carried out as independently as possible from the parents to allow a free, autonomous response.

The questionnaire on *Experience in Social Systems Questionnaire (EXIS)* [48] measures basic dimensions of systems functioning, i.e. accord, belonging, autonomy, and confidence in the future within the last 2 weeks with 12 items. The EXIS shows very good to good internal consistency, and test-re-test reliability, both in the overall value and regarding its dimensions. The EXIS children’s version has been developed with children from the age of 5 and is accompanied by master’s students in psychology. It is carried out as independently as possible from the parents to allow a free, autonomous response.

The *Burden Assessment Scale (BAS)* [4] uses 19 items to assess personal stress, feelings of guilt, the need to interrupt and postpone important matters, and a changed time perspective in connection with the symptoms displayed by the significant other of an ill person within the last 6 months. The BAS shows excellent internal consistency considering its overall score.

The short form of the *Symptom Checklist (SCL-9 k)* [49] measures impairment using nine items on somatization, obsessiveness, social insecurity, depressiveness, anxiety, aggressiveness, phobic anxiety, paranoid thinking, and psychoticism. The SCL-9 K is shown to have good internal consistency and test-re-test reliability on the Global Severity Index (GSI).

The *Witten Resources Questionnaire (WIRF)* [50] measures resources in the three domains of general coping, past difficult situations and current problems, using 12 items each. The WIRF shows good to satisfactory internal consistency in the overall score as well as regarding its dimensions. In our study, we will limit the WIRF to the domain assessing coping with current problems for economic reasons.

The *Development of Psychotherapist Common Core Questionnaire (DPCCQ)* [51–53] characterizes therapists on several subscales [54], of which we chose sociodemographic data, interpersonal style, relational skills, quality of therapists’ personal lives, and difficulties in practice to be suitable for this feasibility study. The scales have been found predictive of the therapeutic alliance and outcome.

Children and significant others will complete a brief *demographic measure*, including age, sex, education level, and whether they are employed.

### Sample size calculation

Assuming an estimated small between-group effect size (80% power, 5% significance level), we will need 344 child-significant other dyads in a confirmatory RCT for direct comparison of INMUT-KB and MUT-K [34]. This calculation grounds in the suggestion of at least 9% of the subsequently powered RCT sample to be seen in the prior feasibility RCT. Consequently, we will recruit at least 32 child-significant other dyads. Taking the WLG into account with an additional one-third of this sample, i.e. 10 child-significant other dyads, and a drop-out rate of, again, an additional 25% in each study arm, i.e. 10 child-significant other dyads in addition, the total sample size for our feasibility RCT will include 52 child-significant other dyads (intention to treat, ITT; INMUT-KB, *n* = 21; MUT-K, *n* = 21; WLG, *n* = 10). The number of participants expected to complete the trial encompasses 40 child-significant other dyads (per protocol, PP; INMUT-KB, *n* = 16; MUT-K, *n* = 16; WLG, *n* = 8).

### Statistical analyses

#### Feasibility and acceptability of research methodology

To analyse the feasibility and acceptability of the research methodology, we will calculate screening, recruitment, randomization, and drop-out rates considering the child and significant other, as well as missing data in the paper–pencil surveys at baseline (pre-T1), post intervention (post-T10), and at 3-month follow-up (cat-T11) (RQ1.1). We will calculate inclusion rates of intervention music therapists and APCI music therapists (RQ1.2, RQ1.3). The success of blind APCI ratings by music therapists, who are part of the study but not the music therapists of the child and significant other (RQ1.3), will be analysed performing Qualitative Content Analysis (QCA) [55] and/or Consensual Qualitative Research (CQR) [56, 57].

#### Feasibility and acceptability of the interventions

The *feasibility and acceptability of the APCI music therapy assessments (T1, T2, T10)* by the study families will be analysed performing QCA [55] and/or CQR [56, 57] on the therapists’ final APCI descriptions (RQ2.1). APCI music therapists’ adherence will be calculated as the percentage *(%)* of treatment components defined by the APCI manual across sessions that will be implemented as planned [58]. It will also be calculated using *Cohen’s kappa* considering the interrater reliability, based on data derived from randomly selected first or second sessions (T1, T2), and finals sessions (T10), evaluated by two independent observers (RQ2.2). To analyse the *feasibility and acceptability of the music therapy interventions (T3–T9)* by the study families, we will calculate mean scores (*M*), standard deviations (*SD*), and 95% confidence intervals (*CI*), in addition to percentages *(%)* considering data gathered on the visual analogue scale, the attempt and completion of the music therapy interventions, and the request for alternative music therapy interventions in the WLG. We will perform QCA [55] and/or CQR [56, 57] to analyse additional data collected on the basis of the study families’ experience-based reports [43] (RQ2.3). Music therapists’ adherence will be calculated as the percentage *(%)* of treatment components defined by the INMUT-KB or MUT-K manual across sessions that will be implemented as planned [58]. It will also be calculated using *Cohen’s kappa* considering the interrater reliability, based on data derived from the independent observers’ evaluation of every third music therapy session (RQ2.4). *Additional benefits and barriers* of INMUT-KB, MUT-K, and WLG will again be calculated by mean scores (*M*), standard deviations (*SD*), and 95% confidence intervals (*CI*), in addition to percentages *(%)*, with respect to intervention safety and potential adverse outcomes. Study families’ experience-based reports on these benefits and barriers will be analysed performing QCA [55] and/or CQR [56, 57] (RQ2.5).

#### Estimation of effect sizes

For *estimation of effect sizes*, and because child-significant other dyads treated by one music therapist (within-group) may be more like each other compared to those treated by another music therapists (within-group), a two-level linear regression analysis will be performed to account for potential clustering effects at higher levels (i.e. child-significant other dyads nested within therapists). The intraclass correlation (ICC) coefficient from the random intercept model with child-significant other dyad (Level 1) and therapist (Level 2) will be calculated for the proposed primary outcome (APCI) [59]. An ICC greater than zero will indicate a clustering effect, and any statistical analysis must be adjusted for these effects. All proposed outcomes will be analysed as intention to treat (ITT; *n* = 52) using mean scores (*M*), standard deviations (*SD*), and 95% *CI*. The ITT calculation will be regardless of whether the child-significant other dyads will violate the inclusion criteria, whether they complete the music therapy, or whether they will withdraw from the study due to protocol deviations (e.g. concurrent music therapy during the study period [60]). Missing values of less than 20% will be replaced with the conditional mean value of the subgroups (INMUT-KB, MUT-K, WLG). This will be compared to per-protocol analyses. We will use mixed-design ANOVAs (group: INMUT-KB, MUT-K, WLG; status: child-significant other dyad, child alone; time: baseline, post-intervention, 3-month follow-up), adjusting for baseline scores considering demography as well as outcome data. Because treatment outcome will be measured at three assessment points, within-group effects will be further analysed by comparisons between baseline and post-intervention (Contrast A) and by comparisons between post-intervention and 3-month follow-up (Contrast B) (RQ3.1). Effect sizes will be presented as partial eta-squared values (η^2^) and Cohen’s *d*, calculated as the difference between the means divided by the pooled standard deviation $$(d=\frac{{x}_{1}^{2}-{x}_{1}^{2}}{\sqrt{{s}_{1}^{2}+{s}_{2}^{2}}/2})$$. Classification of *effect sizes* will be as follows: η^2^ ≥ 0.010, small effect; η^2^ ≥ 0.060, medium effect; η^2^ ≥ 0.140, large effect; Cohen’s *d* 0.20, small effect; *d* ≥ 0.50, medium effect; and *d* ≥ 0.80, large effect [61] (RQ3.2, RQ3.3).

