### Measures

As the purpose of this study is to explore the feasibility of a fully powered RCT, we will use different measures, including both qualitative information and quantitative data.Feasibility and acceptability of research methodology*RQ1.1*: The feasibility analysis of the protocol implementation focusses on the overall recruitment target of the child-significant other dyads (*n* = 52), as well as the specific recruitment target for each study-arm INMUT-KB (*n* = 21), MUT-K (*n* = 21), and WLG (*n* = 10). The study considers the estimation of the total sample to be recruited, the overall dropout rate, and the differentiated dropout rate within the study arms at all measurement times. Data will be collected by observing the participant flow: Counting the number of study participants who (1) are recommended for inclusion by the medical team; (2) are contacted by the study staff to provide information about the feasibility RCT; (3) give their consent to study participation; (4) will be included into the study; (5) drop out before the baseline survey (pre-T1); (6) complete the baseline survey (pre-T1); (7) drop out before or during the baseline APCI ratings (T1/T2); (8) complete the baseline APCI ratings (T1/T2); (9) drop out before or during the INMUT-KB, MUT-K, and WLG (T3–T9); (10) complete INMUT-KB, MUT-K, and WLG (T3–T9); (11) drop out before the final APCI rating (T10); (12) complete the final APCI rating (T10); (13) drop out before the outcome survey (post-T10); (14) complete the outcome survey (post-T10); (15) drop out before the 3-month follow-up survey (cat-T11); and (16) complete the 3-month follow-up survey (cat-T11). We will describe the causes for dropout and calculate the retention rate for the three study arms separately and together. Success is defined as attaining 100% and retaining 75% of the planned sample.*RQ1.2*: The feasibility of this RCT depends on the recruitment of a sufficient number of music therapists. We expect around five to six cases per music therapist, so that successful recruitment will involve at least seven to eight music therapists. For professional support, every third session will be supervised; based on the case numbers, we are planning 108 supervised sessions.*RQ1.3*: Certification to use the APCI was started by seven music therapists and successfully completed by five. The APCI raters were trained in the practical application of the APCI manual, video analysis, data collection, and statistical analysis. Experience-based receptive interviews [43] with APCI raters will gather information about the circumstances that contribute to successful APCI implementation. The success of APCI blinding will also be evaluated in receptive interviews. For professional support, every third APCI session will be supervised; based on the case numbers, we are planning 49 supervised sessions.

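### Arm-mean replacement of missing values below 20% understates SDs and standard errors if whole scores are filled, and the rule stops short of the plan's own expected drop-out

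*Protocol article*

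**What the plan says.** The Estimation of effect sizes section states "All proposed outcomes will be analysed as intention to treat", with n = 52, reported as means, SDs and 95% confidence intervals. Dyads stay in that set regardless of "whether they complete the music therapy, or whether they will withdraw from the study due to protocol deviations". The one rule for incomplete data there is "Missing values of less than 20% will be replaced with the conditional mean value of the subgroups (INMUT-KB, MUT-K, WLG"), and the result is then compared with per-protocol analyses. The sentence does not say whether 20% is a share of items in a questionnaire, of one participant's values, or of the dyads in an arm.

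The Sample size calculation section allows for "a drop-out rate of, again, an additional 25% in each study arm". It gives the randomised numbers as "intention to treat, ITT; INMUT-KB, *n* = 21; MUT-K, *n* = 21; WLG, *n* = 10" and the expected completers as "per protocol, PP; INMUT-KB, *n* = 16; MUT-K, *n* = 16; WLG, *n* = 8". Under RQ1.1 in Measures, "Success is defined as attaining 100% and retaining 75% of the planned sample", so a loss of one quarter still meets the plan's own criterion.

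**The concern.** There are two problems, and they arise at different levels of loss.

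- **Below 20%.** If the rule fills in whole scores, every filled value equals the arm mean. It adds nothing to the spread but raises the count, so the SD, the standard error and the interval shrink, and Cohen's d (mean difference over pooled SD) grows.
- **At 20% or more.** The rule is silent, yet this is where the plan expects to be.

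Effect sizes and 95% intervals are what RQ3 is meant to deliver. The abstract's discussion says the number of dyads for the confirmatory trial will be calculated from the efficacy trends seen here. An inflated d pushes that number down, in a vulnerable population for which the plan itself asks for careful case-number estimation.

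**Working it through.** **Inputs.** Randomised 21/21/10 = 52, completers 16/16/8 = 40, and confirmatory N of 344 (Sample size calculation). Replacement limit below 20%, and d as mean difference over pooled SD (Estimation of effect sizes).

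**1. The plan's own figures.** The build-up is 32 + 10 = 42 dyads; 42 × 1.25 = 52.5, stated as 52. Completers are 16 + 16 + 8 = 40, and 40/52 = 76.9% retained, which agrees with the 75% retention criterion.

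**2. Expected loss against the 20% limit.**

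| Arm | Expected loss | Below 20%? |
|---|---|---|
| INMUT-KB | 5/21 = 23.8% | no |
| MUT-K | 5/21 = 23.8% | no |
| WLG | 2/10 = 20.0% | no |
| Overall | 12/52 = 23.1% | no |

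If each dyad dropped out independently with probability 25%, the binomial chance of a loss of 20% or more would be 63% in a 21-dyad arm, 76% in the WLG and 79% overall.

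**3. Effect of the rule where it applies.** Assume that whole scores are replaced and that the 20% is counted per arm. A 21-dyad arm may then have at most 4 missing (4/21 = 19.0%), because 5/21 is over the limit. Take the replacement value as the mean of the observed dyads in the arm. With k = 17 observed of n = 21:

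- SD factor = √((k − 1)/(n − 1)) = √(16/20) = 0.894
- Between-arm d factor = 1/0.894 = 1.118
- SE factor = 0.894 × √(k/n) = 0.894 × √(17/21) = 0.805
- Coverage of the nominal 95% interval for the arm difference: about 88.6%, against 95% using observed values only. This was simulated with 100,000 two-arm data sets, normal data, equal SDs and values missing completely at random within arm.

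**4. Within-arm pre-post d (RQ3.2, RQ3.3).** With complete baseline data only the post-intervention SD shrinks. The pooled variance factor is (1 + 0.8)/2 = 0.9, so d is multiplied by 1/√0.9 = 1.054, about 5%.

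**5. Consequence for a confirmatory N.** N scales with 1/d², so the factor is 16/20 = 0.80. With 344 as illustration, 344 × 0.80 = 275, which is 20% fewer.

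**6. Against sampling error.** With 21 per arm the SE of a between-arm d is about √(2/21) = 0.31. At an assumed d of 0.30 (the article gives no numeric effect), the inflation is 0.30 × 0.118 = 0.035, about a tenth of that SE.

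**The case against.** **The 20% may mean questionnaire items.** This is plausible. The secondary outcomes are largely multi-item scales, and the analysis text for RQ1.1 speaks of missing data in the paper surveys. On that reading no whole score is filled and the factors in step 3 do not arise. But the sentence comes straight after the description of how non-completers stay in the ITT set, and on the item reading drop-outs have no rule at all. The size of the distortion is therefore conditional; the gap for n = 52 is not.

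**Larger losses may be handled in a fuller document.** Silence alone would be no finding. Here, however, the article states a rule, with a limit that its own expected counts reach or exceed in every arm, next to an ITT size that presumes everyone is analysed.

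**The study is exploratory and per-protocol results will be shown alongside.** Both are true and lower the stakes. A completers' analysis does not repair the ITT intervals.

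**Stronger readings that the article does not support.**

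- A reader might apply the inflation at the planned loss of 5 of 21. The rule excludes that case, so narrowed intervals and the missing rule do not occur together in one arm if the 20% is counted per arm.
- A reader might conclude that every effect size is about 12% too large. RQ3.2 and RQ3.3 ask for within-subject effects, where the figure is about 5%.
- A reader might conclude that the confirmatory trial will be under-sized. The pull is downward, but step 6 shows that sampling error in d is much larger. Under the assumptions used the mean difference itself is unbiased; informative drop-out could shift it either way.
- A reader might say that the mixed-design ANOVA will drop incomplete dyads. That is usual software behaviour, not something the article states.

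**Conclusion.** The point stands in conditional form. If whole scores are replaced, the rule gives SDs and standard errors that are too small. At its limit in a 21-dyad arm the SD is 11% too low, the between-arm d 12% too high and the SE about 20% too low, and coverage is about 88.6% instead of 95%. These figures assume normal data, equal SDs and values missing at random within arm, with the limit applied per arm. A confirmatory N scaled from that d would tend to be about 20% too small from this source alone.

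On any reading that the text allows, the stated rule does not deliver an ITT analysis of 52 at the expected loss: it stops at 20% while the plan's counts give 20.0% to 23.8% by arm, or it concerns items and never covers drop-out. This is a badly fixed rule, not merely an omitted detail.

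**What to change.** 1. Delete arm-mean replacement of outcome scores. If replacement of single items within a scale is meant, say so, state what the 20% is a share of, and confine the rule to that.
2. For all outcomes and at any percentage missing, use a likelihood-based (REML) mixed model. Enter baseline and post-baseline values all as outcomes, with baseline means constrained equal across arms and the therapist random effect already planned. Dyads with only a baseline value then contribute, under missing at random. Entering baseline as a covariate would not achieve this for the APCI. Table 2 schedules it only at T1/T2 and T10, so such a model reduces to ANCOVA on dyads with a T10 score.
3. Alternatively, use multiple imputation by arm, with baseline in the imputation model and Rubin's rules.
4. Compute SDs and Cohen's d from observed values or from the multiply imputed data, and keep the planned per-protocol comparison.

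The cost is analysis wording, slightly more analysis work and wider intervals. Nothing in recruitment, visits or measurement changes.

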**Methods:**

We conducted an assessor blind, prospective, multicentric feasibility randomized controlled trial (RCT) with subsequent intervention. Including overall 52 child-significant other dyads, INMUT investigates interaction-focused music therapy with cancer-affected children and their significant others (INMUT-KB; *n* = 21) compared to music therapy only with the child (MUT-K; *n* = 21) and a wait-list group (WLG; *n* = 10). The measurement points include the screening for a cancer diagnosis, psychometric baseline (pre-T1), initial assessment (T1/T2), music therapy sessions (T3–T9), final assessment (T10), final psychometric evaluation (post-T10), and 3-month follow-up (cat-T11). *Feasibility and acceptability* of the (1) research methodology, (2) intervention and (3) estimation of effect sizes will be assessed using qualitative and quantitative data. The *proposed primary outcome* includes the parent–child interaction (APCI), and the *proposed secondary outcomes* refer to subjective goal achievement (GAS), quality of life (KINDL), system-related functional level (EXIS), psychosocial stress (BAS), psychosomatic complaints (SCL-9k), and resources (WIRF). We plan to investigate the efficacy of INMUT-KB and MUT-K post-intervention (post-T10) within the RCT design and at 3-month follow-up (cat-T11).

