## Methods

### Design

This study is planned as an assessor blind, prospective, multicentric feasibility RCT with subsequent intervention. A total of 52 clients will be randomized to either the newly developed music therapy (INMUT-KB; *n* = 21), the music therapy as usual (MUT-K; *n* = 21), or the wait-list group (WLG, *n* = 10). The intervention outcome will be measured at three assessment points: baseline; post-intervention (primary endpoint), and 3-month follow-up.

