#### Follow-up (cat-T11)

A paper–pencil follow-up survey will be completed 3 months after the last APCI was carried out by all children (approx. 10 to 15 min) and significant others (approx. 20 to 30 min) (cat-T11).

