### Blinding and Allegiance

#### Blinding

The APCI sessions at baseline (T1/T2) and end of therapy (T10), indicating the primary endpoint of this feasibility RCTs, will be blindly conducted by APCI raters. The music therapists will know the assignment as they will also guide the INMUT-KB and MUT-K (T3 to T9). APCI raters will not be the music therapists who are otherwise working with the child-significant other dyads. The included child-significant other dyads will be informed about their assignment and the general aims of the study, but not about specific hypotheses of any endpoint.

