
2.Feasibility and acceptability of the interventions*RQ2.1*: The feasibility and acceptance of the APCI ratings (T1, T2, and T10) by study families are assessed by analysing the therapists’ final APCI descriptions.*RQ2.2*: How well APCI raters implement the APCI ratings (T1, T2, and T10) is assessed by their self-assessment after each APCI session using an APCI manual adherence scale (range: 0 to 100). In addition, randomly selected first or second sessions (T1, T2) and final sessions (T10) are evaluated by two independent observers.*RQ2.3*: The feasibility and acceptance of the music therapy interventions (T3–T9) by study families are assessed on a visual analogue scale (range: 0 to 100), complemented by experience-based reports in receptive interviews [43] conducted with the study families during the study period. In particular, the needs of the child-significant other dyads are analysed with a special focus on the involvement of significant others in the music therapy process. Compliance with the INMUT-KB and MUT-K conditions by the children and significant others is assessed based on the percentage of attempted and completed music therapy sessions. Compliance with the WLG is assessed according to whether alternative music therapy interventions outside the trial were used during the waiting period.*RQ2.4*: How well music therapists implement the music therapy interventions (T3–T9) is assessed by their self-assessment after each session using an intervention manual adherence scale (range: 0 to 100). In addition, every third session is evaluated by two independent observers.*RQ2.5*: Additional identified benefits and barriers of INMUT-KB, MUT-K, and WLG will be monitored throughout the study and considered in relation to intervention safety and potential adverse outcomes, in addition to experience-based reports in receptive interviews [43]. For any undesirable psychological and/or somatic effects during or after the music therapy interventions, psychological psychotherapists at the Centre for Mental Health and Psychotherapy (ZPP) at the UW/H, directed by [name]. [name], will be available.

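### The effect-size model keeps the wait-list group as a comparison arm at the 3-month follow-up, although the text suggests, without dating it, that this group may already be in therapy by then

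*Protocol article*

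**What the plan says.** The analysis model is set out under Statistical analyses, Estimation of effect sizes: "We will use mixed-design ANOVAs (group: INMUT-KB, MUT-K, WLG; status: child-significant other dyad, child alone; time: baseline, post-intervention, 3-month follow-up". The same paragraph defines two within-group contrasts, A (baseline to post-intervention) and B (post-intervention to follow-up), and exempts no arm from either.

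Five other places bear on what the WLG is doing at follow-up:

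- **Design:** "This study is planned as an assessor blind, prospective, multicentric feasibility RCT with subsequent intervention".
- **Measures, RQ1.1 (participant flow):** dyads are counted who "drop out before or during the INMUT-KB, MUT-K, and WLG" in the window T3–T9. The next item counts those who complete these three conditions in the same window. T10, post-T10 and cat-T11 come afterwards.
- **Abstract, Methods:** "We plan to investigate the efficacy of INMUT-KB and MUT-K post-intervention (post-T10) within the RCT design and at 3-month follow-up (cat-T11").
- **Measures, RQ2.3:** "Compliance with the WLG is assessed according to whether alternative music therapy interventions outside the trial were used during the waiting period".
- **Follow-up (cat-T11):** the "follow-up survey will be completed 3 months after the last APCI was carried out by all children" and significant others. WLG is not excepted.

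**The concern.** A wait-list arm can serve as an untreated control only while it is waiting. If its dyads start their own music therapy after post-T10 and before cat-T11, two results would mislead. A lasting benefit of INMUT-KB or MUT-K would appear to fade relative to WLG because WLG is catching up. And Contrast B within WLG would contain a treatment gain that a reader could take for the natural course.

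The article intends to judge from this trial's efficacy trends whether a confirmatory trial is worth the investment (Abstract, Discussion). It plans to include a waiting group again (Perspectives of a confirmatory trial). A distorted follow-up pattern would feed into that judgement.

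**Working it through.** **1. When does the wait end?**

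- The participant-flow list gives the WLG condition the same window as therapy, T3–T9, and treats it as completed before T10.
- The Design label says that an intervention follows the RCT. In a trial with a wait-list arm, the natural meaning is that this arm is treated afterwards. The phrase is never defined.
- The Abstract links the randomised design to post-T10 and names cat-T11 separately.
- The compliance rule treats the wait as a bounded period and looks for music therapy obtained elsewhere during it.

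Together these favour a wait that ends around T10 or post-T10, with WLG therapy following. None of them gives a start date, so treatment before cat-T11 is the better reading and not an established fact.

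**2. Which outcomes are exposed?**

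Table 2 schedules the APCI at T1/T2 and T10 only. The Blinding section agrees: it places the rated sessions that form the primary endpoint at those same times and mentions none at cat-T11. The Design section gives the assessment times as "baseline; post-intervention (primary endpoint), and 3-month follow-up". At cat-T11 only the questionnaires and goal attainment are collected (GAS, KINDL, EXIS, BAS, SCL-9k, WIRF). The exposure is therefore confined to these secondary outcomes.

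**3. How large could the distortion be?**

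The article gives no figure for therapy versus waiting, so this is an illustration. Assumptions: therapy exceeds waiting by d at post-T10; the gain is fully kept to cat-T11; there is no other change over time; and WLG has gained a share f of the same benefit by cat-T11.

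- Treated minus WLG at post-T10: d − 0 = d
- Treated minus WLG at cat-T11: d − f·d = d(1−f)
- Contrast B within WLG: f·d − 0 = f·d

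| f | d(1−f), d = 0.2 | d(1−f), d = 0.5 | d(1−f), d = 0.8 | WLG Contrast B, d = 0.5 |
|---|---|---|---|---|
| 0 (WLG treated after cat-T11) | 0.20 | 0.50 | 0.80 | 0 |
| 0.25 | 0.15 | 0.375 | 0.60 | 0.125 |
| 0.5 | 0.10 | 0.25 | 0.40 | 0.25 |
| 0.75 | 0.05 | 0.125 | 0.20 | 0.375 |
| 1 | 0 | 0 | 0 | 0.50 |

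The three-time group-by-time effect size draws on the follow-up column as well as post-T10, so it inherits part of this shift.

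**4. How precise is the comparison in any case?**

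The allocation is 21 + 21 + 10 = 52, so WLG is 10/52 = 19% of the sample. The approximate 95% half-width for d of one treated arm against WLG is 1.96·√(1/n₁ + 1/n₂):

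- As randomised: 1.96·√(1/21 + 1/10) = 1.96 × 0.384 = 0.75
- Expected completers: 1.96·√(1/16 + 1/8) = 1.96 × 0.433 = 0.85

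The comparison is imprecise whether or not WLG has been treated.

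**The case against.** A reader might infer that WLG dyads have definitely crossed over by cat-T11. The documents do not support that. No sentence dates their therapy, the patient flow is in Fig. 1, which is not shown, and an article need not repeat everything in the full protocol. If WLG is treated only after cat-T11, f = 0 and the comparison is sound.

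Nor would a wait lasting to cat-T11 strictly contradict the Abstract or the participant-flow list. T3–T9 can be read as a common counting window for all arms, and the Abstract does not say when WLG is treated.

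One might also fault the Follow-up section for timing the survey from the last APCI. That does not stand: Table 2 ties cat-T11 to three months after T10, and the Outcome section calls T10 the final APCI session.

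The stakes are limited too. RQ3.2 and RQ3.3 ask for change from baseline to the end of therapy. RQ3.1 and the figure of 344 dyads concern INMUT-KB versus MUT-K. All analyses are declared descriptive and exploratory, and the article nowhere interprets the WLG's Contrast B as natural recovery.

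All of this stands and narrows the point. It does not remove it. The article does more than leave a detail unsaid: it specifies a model that uses WLG at all three times, without the condition that would make this valid. Imprecision does not excuse a systematic shift in what is being estimated.

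**Conclusion.** The point holds in conditional form. The stated model uses WLG as a comparison arm at cat-T11, while the text leans towards a wait that ends before then. If WLG therapy starts before cat-T11, the treated-versus-WLG difference at follow-up and the three-time group-by-time effect sizes for the questionnaire outcomes no longer contrast treated with untreated dyads. The possible loss runs from none (therapy after cat-T11) to the whole difference (full catch-up). Both the effect and the catch-up share are assumptions.

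The APCI, the comparison at post-T10 and INMUT-KB versus MUT-K at any time are unaffected. No sample size changes. The point is modest in weight, but it should be settled before the follow-up data are analysed.

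**What to change.** In Estimation of effect sizes:

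1. Limit every analysis that includes WLG to baseline and post-T10.
2. At cat-T11, make the between-group analysis INMUT-KB versus MUT-K only.
3. Report WLG data after post-T10 descriptively, outside the randomised comparison, and exclude WLG from Contrast B as a comparative result.
4. State when WLG receives its intervention relative to cat-T11. Keep WLG in the model at cat-T11 only if the protocol states that its therapy starts after that assessment.

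The definition of cat-T11 needs no change. The cost is wording in the analysis paragraph, with no change to sample size or data collection. The small downside is that no wait-list control is claimed at 3 months.
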